### 2.1. Study Design

The DINISAS project is a multicenter, randomized, cross-over study aimed at analyzing the validity of a HRP in children with suspected OSA compared to overnight PSG performed in the sleep laboratory. This analysis will be performed using blinded outcome assessments, and the project was initiated in 2014. 

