#### 2.2.2. Randomization and Follow Up

All selected children will undergo randomization as follows: Group 1 will be children who whose initial diagnostic test will be home polygraphy (HPR) followed by in-lab PSG; and Group 2 will include children whose initial testing will be in-lab PSG, subsequently followed by HRP. Time interval between the two tests, HRP and PSG, will always be less than one week. Therapeutic decisions (surgical adenotonsillectomy (T&A), continuous positive airway pressure (CPAP), orthodontics, or medical treatment) will be based on the apnea-hypopnea index derived from the HRP, with all PSG results being invisible to both investigators and participating subjects. An independent Safety Monitoring Board with extensive expertise in pediatric OSA was appointed and reviewed both HRP and PSG and if decisions regarding the specific subject based on HRP were inappropriate, the correct intervention was provided (i.e., surgery vs. no surgery).

An overnight in-lab PSG will be performed in all randomized OSA children six months after treatment or simply as a follow-up if no treatment was provided.

Questionnaires and urine tests were conducted in the morning following PSG testing. 

Flow chart of randomization procedures and follow-up of children are shown in Figure 1.

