## 3. Statistical Analysis

All data will be collected in an electronic Case Report Form (eCRD).

Sample size: We estimated a prevalence of 60% of symptomatic children with an AHI > 3 events/h. Thus, a total of 320 eligible subjects are needed assuming a 10% attrition, and a difference in effectiveness between PSG and HSP that will not exceed 9% (α = 0.05 and a β coefficient of 90%). Subjects who refuse to participate and those identified as ineligible will be recorded.

Cost effectiveness analysis is proposed as a non-inferiority study, comparing baseline PSG and 6-month follow-up PSG derived AHI (alpha 0.05; 80% power). It is assumed that the non-inferiority limit is 0.45 units of AHI, i.e., the PSG AHI at 6 months follow-up for therapeutic decisions made with either the PSG or the HPR findings, with a cut-off AHI set at 3.6 ± 2.0 events/h [38]. Considering attrition, 155 subjects will be required to complete the study in each arm (PSG and HPR).

Data will stored in a networked Deductive Database (BBDD) specifically designed and maintained for the study to this study. Statistical analysis will be performed with SPSS package (IBM, New York, NY, USA version 22.0). The measure of the overall agreement between the different categories of the AHI as measured by PSG and HRP, in their automatic and manual analysis, will be assessed by establishing the diagnostic accuracy of the scores obtained by each of the systems. Different categories will be established according to the OSA diagnostic criterion cut-off (AHI > 3 events/h). The HRP discriminatory capacity for the diagnosis of exclusion and confirmation of OSA will be estimated according to different severity AHI cut-off values using ROC curves, area range under the curve and subsequent Bayesian analysis, as previously reported [15,68]. Therapeutic decisions made with PSG will be compared with decisions made with HPR, with data being interpreted independently by all participating centers and compared with each other using Cohen’s Kappa. Further analyses will be carried out on both arms based on intent to treat. In cases considered as attrition, imputation values will be allocated using multiple regression.

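### The arms named in the analysis section (PSG and HPR) are not the randomised groups, which differ only in test order, and no stated analysis clearly uses that order.

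*Protocol article*

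**What the plan says.** Protocol article, section 2.1, describes a "multicenter, randomized, cross-over study aimed at analyzing the validity of a HRP in children with suspected OSA". Section 2.2.2 defines one group by starting at home: "Group 1 will be children who whose initial diagnostic test will be home polygraphy (HPR) followed by in-lab PSG". The other group has the same two tests in reverse order: "Group 2 will include children whose initial testing will be in-lab PSG, subsequently followed by HRP". On timing it says "Time interval between the two tests, HRP and PSG, will always be less than one week". In the same section treatment decisions, for all children, "will be based on the apnea-hypopnea index derived from the HRP", with PSG results hidden and a safety board able to correct a decision.

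Section 3 plans these analyses:
- Agreement, where the target is "The measure of the overall agreement between the different categories of the AHI as measured by PSG and HRP". The method, for automatic and manual HRP scoring alike, is that it "will be assessed by establishing the diagnostic accuracy of the scores obtained by each of the systems".
- ROC curves with a Bayesian analysis.
- Cohen's kappa for therapeutic decisions.
- An analysis by arm: "Further analyses will be carried out on both arms based on intent to treat".

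The only place in section 3 that says what the arms are is the cost-effectiveness sample size. It asks for 155 completers per arm, labels the arms PSG and HPR, and contrasts six-month AHI after decisions made on one test or the other. None of the analyses mentions order, period or sequence.

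**The concern.** Intent to treat means analysis by allocation, and the only allocation here is to a test order. If the arms are PSG and HPR, each child belongs to both, so there is no allocation to preserve. If the arms are the order groups, the label in section 3 is wrong. The cost-effectiveness contrast cannot be read off them either, because both groups are treated on the same test. A reader given an intent-to-treat comparison of PSG and HPR arms would take it as a randomised comparison of two care strategies, which section 2.2.2 does not create.

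The second part follows from the first. Order was randomised so that a first-to-second-test change could be separated from a difference between devices. The introduction itself says that the laboratory is unfamiliar, can cause anxiety and can alter sleep architecture, so some effect of which night comes first is plausible. Balanced order removes such a shift from the mean HRP–PSG difference. It does not remove it from classification around a cut-off, and pooled results alone would not show it.

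**Working it through.** **1. The two sections side by side.**
- Section 2.2.2: two groups, each child tested with both devices, order randomised, treatment based on HRP in both groups.
- Section 3: two arms named after the tests, decisions made on either test, intent to treat on both arms.

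These cannot both describe the same groups.

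**2. What the plan's own numbers imply about the arms.**
- Margin 0.45, SD 2.0, 80% power, one-sided 0.025. The one-sample or paired formula gives (2.0 × (1.960 + 0.842)/0.45)² = 155.04, which matches the stated 155 with no attrition added.
- Two independent arms would need twice that, 311 per arm (245 at one-sided 0.05).
- If the arms were separate groups, 2 × 155 = 310 completers would be needed. The 320 children with 10% attrition leave 320 × 0.9 = 288, or 144 per order group at an assumed 1:1 allocation.

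The sample size text therefore does not settle what an arm is.

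**3. What an order shift would do (illustration).**

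Inputs:
- AHI normal with mean 3.6 and SD 2.0. The figures are in section 3, but the article does not give them as the baseline distribution, so their use here is an assumption.
- Correlation between the two tests in the same child 0.75 (assumption).
- Cut-off AHI > 3 (section 3).
- Second test shifted by d = 0.5 events/h (assumption).
- Orders 1:1 and no true device bias (assumptions).

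No shift:
- Each test is positive with probability 1 − Φ((3 − 3.6)/2) = 0.618.
- From the bivariate normal, both positive 0.508 and both negative 0.272, so observed agreement is 0.781.
- Chance agreement is 0.618² + 0.382² = 0.528.
- Kappa = (0.781 − 0.528)/(1 − 0.528), about 0.53 to 0.54. Sensitivity 82%, specificity 71%.

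Shift d = 0.5. In each order group: both positive 0.5527, both negative 0.2259, only the second test positive 0.1561, only the first positive 0.0652.
- HRP-first (PSG is second): sensitivity 0.5527/(0.5527 + 0.1561) = 78%; specificity 0.2259/(0.2259 + 0.0652) = 78%.
- PSG-first (HRP is second): sensitivity 0.5527/(0.5527 + 0.0652) = 89%; specificity 0.2259/(0.2259 + 0.1561) = 59%.
- Pooled: mean difference (−0.5 + 0.5)/2 = 0. Positive rate 0.663 for each test, agreement 0.779, chance agreement 0.663² + 0.337² = 0.553, kappa 0.50. Sensitivity 83%, specificity 67%.

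Other shifts, same model:

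| Shift | Pooled kappa | Pooled sens. | Pooled spec. |
|---|---|---|---|
| −1.0 | 0.44 | 73% | 71% |
| −0.5 | 0.51 | 79% | 72% |
| 0 | 0.54 | 82% | 71% |
| +0.25 | 0.53 | 83% | 70% |
| +0.5 | 0.50 | 83% | 67% |
| +1.0 | 0.42 | 83% | 60% |

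At −0.5 sensitivity is 86% (HRP-first) against 73% (PSG-first).

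A log-normal version (60% above 3, total log-SD 1.0, within-child log-SD 0.3 to 0.5) with a second-test fall of about 18% agrees. Pooled kappa drops from 0.73 to 0.70, or from 0.54 to 0.52. Sensitivity by order is 0.93 against 0.81, or 0.85 against 0.74.

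**4. Could the trial see it?** The SD of the paired difference within an order is √(2 × 2.0² × 0.25) = 1.41. The mean HRP–PSG difference differs between orders by 2d, so the standard error of d is (1.41/2) × √(2/144) = 0.083. A shift of 2.80 × 0.083 = 0.23 events/h is detectable with 80% power. By-order accuracy is less precise. At d = 0.5 the 95% half-width for the difference between orders is about 10 points for sensitivity (about 102 and 89 PSG-positive children) and about 18 points for specificity (about 42 and 55 PSG-negative).

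**The case against.** The strongest reply is that this is a condensed article. A period term or a table by order is the kind of detail left to a full protocol or analysis plan, and section 3 nowhere says that order will be ignored. The phrase about both arms could even mean the two order groups. This stands: the missing order term alone would be a weak point, and the most that can be said is that no stated analysis clearly uses order. It does not remove the mismatch between sections 2.2.2 and 3, which is in the text shown. If the order groups are meant, the label in section 3 is still wrong.

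It is also fair that randomised order and the short interval already protect the mean difference, that nothing in the article gives the size or sign of a shift, and that a normal AHI with these figures puts 3.6% of children below zero. With 288 completers, about 40% of them below the cut-off, the 95% half-width for pooled specificity is about 8 points. That is twice the 4-point fall at a shift of 0.5.

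Stronger readings are tempting and are not supported:
- A reader might infer that pooling hides HRP error. Under the model above, a shift lowers kappa and widens the paired differences, so pooled agreement makes HRP look worse, not better.
- A reader might infer that limits of agreement would be distorted. The article plans none.
- A reader might take the kappa figures as the planned kappa. The planned one is for therapeutic decisions, while the figures here are for AHI above or below 3.
- A reader might infer that pooled sensitivity and specificity both deteriorate. Pooled sensitivity barely moves for upward shifts, and pooled specificity barely moves for downward ones.

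**Conclusion.** The point holds as an inconsistency with a modest analytic consequence. The randomised groups are HRP-first and PSG-first. Section 3 describes arms called PSG and HPR and promises intent-to-treat analyses on them. As written, those analyses cannot be carried out on the randomised groups, and their result could be mistaken for a randomised comparison of PSG-guided with HRP-guided care. This conclusion needs no assumptions.

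The size of an order effect does rest on assumptions: the AHI distribution, reliability 0.75, 1:1 order and an invented shift. With a shift of 0.5 events/h, the pooled mean difference is unaffected and pooled kappa moves by about 0.03. Apparent HRP sensitivity differs by about 11 points between orders and specificity by about 18. The case for using order is that this difference would otherwise go unseen and that looking for it costs nothing. The documents do not show that the pooled results would be seriously wrong.

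**What to change.** - Reconcile sections 2.2.2 and 3. Name the randomised groups HRP-first and PSG-first, and state which groups the intent-to-treat sentence and the 155 per arm refer to.
- Do not present an intent-to-treat comparison of the order groups as PSG-guided against HRP-guided care. If that contrast is wanted for cost-effectiveness, say how it is built from children who all have both tests, and that it is not a randomised comparison.
- Estimate the period (order) effect from the paired HRP–PSG AHI differences and report it with its interval.
- Report diagnostic accuracy and the decision kappa by randomised order beside the pooled values, as description with intervals, since the by-order estimates are imprecise.

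The cost is a few sentences of analysis text. Order is known from the randomisation, no new data are needed, and the sample size is unchanged.

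### Regression-predicted values for attrition cases, if counted as observed data, would make the 6-month non-inferiority test modestly too lenient

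*Protocol article*

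**What the plan says.** The rule is one sentence at the end of the analysis paragraph in section 3: "In cases considered as attrition, imputation values will be allocated using multiple regression". It follows the sentence that announces intent-to-treat analyses of both arms, which in turn follows the accuracy, ROC and kappa plans. It names no predictors, number of draws, residual term or pooling rule, and it does not say which variables or analyses it covers.

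Two sets of figures in section 3 bear on it:

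- **Diagnostic comparison.** "We estimated a prevalence of 60% of symptomatic children with an AHI > 3 events/h". The size statement is "a total of 320 eligible subjects are needed assuming a 10% attrition".
- **Cost-effectiveness comparison.** It is framed as non-inferiority, "comparing baseline PSG and 6-month follow-up PSG derived AHI (alpha 0.05; 80% power". The article assumes that "the non-inferiority limit is 0.45 units of AHI", "with a cut-off AHI set at 3.6 ± 2.0 events/h", and requires 155 children per arm.

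Section 2.2.2 puts the two baseline tests less than a week apart and schedules a PSG at six months. Section 2.4.2 has an invalid HRP or PSG repeated within 7 days.

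**The concern.** A regression prediction is a conditional mean. Put into the data set as a child's AHI, it lies exactly on the fitted line and adds to the sample size as if it had been measured. Two errors follow. The spread of the filled-in outcome is too small, and the denominator counts children who gave no outcome. Both shrink the reported standard error. In a superiority trial that produces false differences. In a non-inferiority comparison it narrows the interval around the HRP-PSG difference, so the 0.45 limit is cleared too easily.

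The open scope raises a second question. The main objective in the Introduction is the diagnostic validity of HRP against PSG. If a missing baseline test were filled in, a predicted value would enter the accuracy and agreement estimates as a test result.

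**Working it through.** **Inputs from section 3.** N = 320; attrition m = 0.10; prevalence 0.60 above AHI 3; margin 0.45; ±2.0 read as the SD; 155 per arm; alpha 0.05 with sidedness not stated.

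**Assumptions not in the article.** Data missing completely at random; predictors explain a share R² of 0 to 0.5 of the 6-month AHI variance; two independent arms with equal m and R², and a regression that respects arm; HRP-PSG correlation 0.5 to 0.85.

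**Step 1: the plan's own figures.** 320 × 0.10 = 32 children, which leaves 288; 288/0.90 = 320. The formula behind 320 is not given and is not disputed here. The figure of 155 is returned by the one-sample or paired formula at two-sided 0.05 and 80% power: (2.0 × (1.960 + 0.842)/0.45)² = 155.04 with unrounded quantiles, before attrition. Two independent arms would need 311 each (245 at one-sided 0.05). Sample size is a separate matter. It matters here only because it shows that the two-arm reading is an assumption.

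**Step 2: standard error after fill-in.** For a mean over n children with outcome variance σ²:

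- Reported variance, filled-in values treated as data: (σ²/n) × [(1 − m) + m·R²]
- True variance of the filled-in mean: (σ²/n) × [(1 − R²)/(1 − m) + R²]
- SE ratio, reported to true: √{[(1 − m) + m·R²] / [(1 − R²)/(1 − m) + R²]}

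With equal arms the same ratio applies to the difference. The actual type I error is the normal tail area beyond z × ratio.

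| R² | Reported factor | True factor | SE ratio | Error at one-sided 5% | Error at one-sided 2.5% |
|---|---|---|---|---|---|
| 0 | 0.90 | 1.111 | 0.90 | 6.9% | 3.9% |
| 0.3 | 0.93 | 1.078 | 0.93 | 6.3% | 3.4% |
| 0.5 | 0.95 | 1.056 | 0.95 | 5.9% | 3.1% |

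For example, at R² = 0.3: √(0.93/1.078) = 0.929, and 1.645 × 0.929 = 1.528, with tail area 0.063. Simulation with 155 per arm, SD 2.0 and margin 0.45 agreed with the formula. Complete-case analysis stayed at about 5% under the same assumptions.

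**Step 3: in AHI units.** Take 155 per arm, 10% of them missing, SD 2.0 and R² = 0.3. The full-data SE is 2.0 × √(2/155) = 0.227. The reported SE is 0.227 × √0.93 = 0.219, and the true SE is 0.227 × √1.078 = 0.236. The one-sided 95% half-width is then 0.360 reported against 0.388 true, a gap of about 0.03 against a limit of 0.45.

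**Step 4: direction of distortion if baseline tests were filled in.** Simulation of 320 children with 10% missing, kappa at the AHI 3 cut-off:

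| Correlation | Complete cases | PSG predicted from HRP | PSG predicted from unrelated or weak (r = 0.3) covariates |
|---|---|---|---|
| 0.5 | 0.33 | 0.37 | 0.30 to 0.31 |
| 0.7 | 0.49 | 0.53 | 0.45 to 0.46 |
| 0.85 | 0.64 | 0.67 | 0.59 to 0.60 |

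When PSG is predicted from HRP, 90 to 98% of filled-in pairs agree, against 68 to 83% of real pairs. Adding a residual draw returns kappa to the complete-case value. These figures show direction only: section 3 assigns Cohen's kappa to therapeutic decisions, which were not simulated.

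**The case against.** The strongest reply is that the article does not say single imputation. It names a regression method, and a condensed article may leave the mechanics to a full protocol or analysis plan that is not shown. This stands in part: single fill-in is the plain reading and not the stated one. But the article publishes a method, and as worded that method is not multiple imputation. The point is therefore about a stated choice and not about missing detail.

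A reader might go further and infer that the rule manufactures agreement between HRP and PSG, or biases every comparison. The article does not support that, for these reasons:

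- No predictors are named, and step 4 shows that kappa can fall as well as rise.
- The baseline tests are under a week apart and invalid ones are repeated, so losses should fall mainly on the 6-month PSG. The 10% added to the 320 is a recruitment allowance and does not show that 32 baseline pairs will be filled in.
- The sentence follows the one on intent-to-treat analysis of both arms, so it attaches most naturally to those analyses.
- Only analyses that contain filled-in values are affected.

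It can also be said that the arm structure is unclear, since section 2.2.2 bases treatment on HRP for all children. That stands, and it is why the two-arm reading is listed as an assumption. The ratio in step 2 is also that of a single mean, so a within-child reading would change what R² refers to but not the formula.

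**Conclusion.** The point holds for the 6-month comparison, and its size is modest. If regression predictions are counted as observed at 10% attrition, the standard error is about 5 to 10% too small. A one-sided 5% test then runs at 5.9 to 6.9%, and a one-sided 2.5% test at 3.1 to 3.9%, in favour of declaring non-inferiority. This rests on reading the rule as single fill-in, on two independent arms, on data missing completely at random and on R² between 0 and 0.5. Under those conditions the planned rule controls error less well than no imputation at all.

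For the baseline accuracy and agreement analyses the conclusion is conditional. The wording does not exclude filling in a test result, and doing so would distort the estimates in a direction that depends on the predictors. The article does not say that this will be done. The rule should be changed, but it does not undermine the design.

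**What to change.** Replace the imputation sentence with two statements:

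- Accuracy, ROC and agreement analyses use children with both tests observed and valid. Missing or invalid tests are counted and reported as non-diagnostic, and are not imputed.
- Missing 6-month outcomes and costs are handled by proper multiple imputation, with both parameter and residual draws and variances pooled by Rubin's rules. The predictors are named: baseline AHI and other covariates already collected.

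The number of imputed data sets, and a sensitivity analysis that shifts the imputed values against HRP, are optional. The change needs no extra children or data. It costs a sentence or two, a little computing and slightly wider intervals.

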## 4. Study Significance

Currently, the gold standard approach to the diagnosis of OSA in children remains a PSG in the laboratory [12]. However, the emergence of a large array of home-based technologies and the successful implementation of HST in adults has prompted substantial interest in expanding the role of HST to the pediatric population. Such need is all the more pressing considering on the one hand the elevated prevalence of children who habitually snore and are therefore at-risk for OSA [69,70,71,72,73], and on the other hand the paucity of pediatric sleep laboratories, the scarcity of pediatric sleep medicine physicians, the inconvenience for the child and their family, the high costs in labor, and of the facilities underlying PSG testing. However, HST approaches are not yet extensively validated in children, and their usefulness and financial advantages have not been thoroughly explored despite the relatively large number of published studies comparing PSG and HST.

The proposed study incorporates not only the validation in a real life setting of a HST approach as a diagnostic tool, but also includes an assessment of its robustness in the clinical decision making of when to provide clinical treatment and when to abstain from a therapeutic intervention. Furthermore, it will examine not only the comparative outcomes obtained with HST and PSG, but will also evaluate cognitive outcomes as illustrated by a declarative memory test [65]. In addition, it will provide estimates of feasibility of automatic scoring that should alleviate the laborious burden of manual scoring of HST in children. Importantly, economic assessments of the HST relative to the PSG will be conducted.

Finally, a simple and non-invasive method such as the proposed examination of exosomal miRNAs as biomarkers of OSA in children, and also as biomarkers of cognitive deficits may further advance the field of biomarkers in sleep medicine [46], while enabling initial steps for a convenient diagnostic tool in children with suspected OSA that also carries enabling elements of precision medicine [74,75,76].

